##### Lower-body muscular function

The force–velocity relationship and the rate of force development (RFD) will be assessed unilaterally on a horizontal leg press machine (Selection MED, Technogym, Italy) instrumented with a force plate (Type 9286BA, Kistler, Switzerland) and a linear position transducer (TForce System, Ergotech, Spain). A familiarization session will be performed on the first day of assessments. During the RFD test, participants will receive instructions to execute multiple maximal voluntary isometric contractions. They will be required to rapidly and forcefully extend their knee while maintaining the contraction for 3 s following the cue *"Ready, set, go!"* [48].

Four adequate trials (avoiding countermovement before contraction onset), separated by 60 s will be acquired alternatively (knee angles of 90º and 120º). The maximal isometric force and RFD will be calculated as the linear slope of the time-force curve over different time intervals (0–400 ms) and at the maximal point of the time-RFD curve (RFDmax) [49]. To assess the force–velocity relationship, participants will perform a progressive loading test (5–20 kg increments) with 2 repetitions per load (leaving a few seconds between repetitions to ensure peak performance on the subsequent repetition), starting at approximately 40% of the individual one repetition maximum (1-RM) (corresponding to the first load in which there is no flight phase) until reaching a load equivalent to 80% 1-RM. Loads will be interspersed by 1-min of passive recovery. From the starting position (90º knee angle), participants will be instructed to perform the concentric phase of each repetition as fast and as strong as possible, regardless of the load used. The values of force and velocity of the most powerful repetitions with each load will be fitted by a linear model through the Excel spreadsheet of Alcazar et al. [50] from which we will estimate the theoretical maximal isometric force and the maximal velocity without load (intercepts of force and velocity, respectively). In addition, we will estimate the maximum muscular power as well as the force and velocity at which it is produced [51].

#### Secondary outcomes

##### Upper-body muscular function

Handgrip strength will be assessed on both arms using a digital hand-held dynamometer (Takei TKK5401, Tokyo, Japan), with the handle individually adjusted to fit each participant´s hand. Participants will be seated in a chair with their arm extended and forearm in a neutral position, holding the dynamometer in a vertical position. Before performing the test, the assessor will demonstrate and hand over the dynamometer to the participant for familiarization [52]. After the starting cue, the subject will be encouraged to squeeze as strongly as possible during a 3-s isometric contraction without additional body movement. There will be a 1-min rest between each repetition. The same procedure will be repeated for the opposite hand. Two attempts will be performed, and the maximum value will be chosen.

##### Physical function

Firstly, the Senior Fitness Test (SFT) will be conducted, which includes 6 functional tests: (1) 30-s chair stand test for lower-limb strength, (2) 30-s arm curl test with a 2.5-kg or 4-kg dumbbell for upper-limb strength, (3) 6-min walk test for aerobic endurance, (4) chair sit-and-reach test for lower-limb flexibility, (5) back scratch test for upper-limb flexibility and (6) 8-foot up-and-go test for agility/dynamic balance [37, 53]. Secondly, the Short Physical Performance Battery (SPPB) will be performed to evaluate static balance in feet side-by-side, semi-tandem, and tandem positions, 4-m-usual walking speed, and 5-repetition sit-to-stand test [54]. Additionally, the maximum speed when walking 10 m [55, 56] and the usual speed when walking 3, 6, and 10 m [57] will be also examined. All tests will be performed once, except the walking tests, which will be performed twice. The best value will be chosen in the maximum speed test and the average in the usual walking speed tests.

##### Cardiorespiratory function

A graded exercise test (GXT) and a verification test (VerT) will be conducted using an incremental and a supramaximal test, respectively [58]. Both tests will be performed on an electrically braked cycle ergometer (800S, Ergoline, Bitz, Germany). Oxygen consumption and carbon dioxide production will be evaluated breath by breath using indirect calorimetry (Quark RMR, COSMED, Rome, Italy). A standard 12-lead electrocardiogram (12SL-ECG, GEhealthcare, Finland) will be performed at rest and during exercise to assess the heart’s electrical activity. For the GXT, after a 3-min warm-up at 15W for men and 10W for women, the workload will be increased 1W/7 s for women (8.5W/minute) and 1W/5 s for men (12W/minute) until volitional exhaustion. These increment rates have been designed to bring subjects to exhaustion in 8 to 12 min [59]. Subjects will receive verbal encouragement to reach their maximum effort. Upon reaching exhaustion, the workload will decrease to 10W, and active recovery will be performed by pedaling for 3 min. After 10 min of passive seated rest, participants will complete a constant-load VerT, which consists of a 1-min warm-up at 50% of the maximal workload achieved during the GXT (Wmax),followed by an increase in workload up to 110% Wmax [58]. Verbal encouragement will be given to achieve maximum pedaling time to exhaustion. The test will end when the cycling cadence drops below 45 rpm for 10 consecutive seconds.

##### Blood pressure and heart rate

Resting blood pressure and heart rate will be assessed using a digital upper-arm blood pressure monitor (OMRON M6 Comfort, Omron Healthcare, Kyoto, Japan) [60]. Subjects will be asked to sit in a quiet room for 10 min before the assessments. The selection of cuff size will be chosen according to the left arm circumference of each participant; the blood pressure cuff will be placed on bare skin. Blood pressure will be assessed in a seated position at the level of the right atrium, with the participant’s back supported and uncrossed legs with both feet on the floor. A second separated measurement will be done after a 5-min seated rest period [61].

##### Anthropometry

Subjects’ height and body mass will be measured with a stadiometer and scale device (Seca 711, Hamburg, Germany) to the nearest 0.1 cm and 0.1 kg, respectively. The subject will be barefoot and wearing as minimal clothes as possible. The neck will be kept in a natural unstretched position, with the heels touching each other with the fingertips separated to form a 45° angle and the head held straight with the lower orbital rim in the Frankfort plane [62]. Body mass index will be calculated as body mass (kg) divided by height (m) squared (kg·m^−2^). In addition, the perimeters of the neck, waist, and hip will be measured [63, 64]. The neck circumference will be assessed by placing the tape measure around the neck below the Adam's apple. Waist circumference will be measured by positioning the tape at the midpoint of the last palpable rib and the top of the hip bone. For hip circumference, the measuring tape will be wrapped around the maximum circumference of the buttocks and below the iliac crest. The subject will be asked to inhale air and perform the measurement at the end of a normal exhalation.

##### Body composition

For the determination of bone mass and body composition, 4 densitometry scans will be performed on each subject using a calibrated dual-energy X-ray absorptiometry (DXA, Hologic Series Horizon-A, Bedford, United States). Lean mass (kg), fat mass (kg), bone mineral content (BMC, g), and bone mineral density (BMD, g·cm^−2^) will be assessed in the total and appendicular analysis of the whole-body scan. In addition, BMC and BMD will be assessed in the non-dominant forearm, the proximal region of the right femur (total hip, femoral neck, intertrochanter, greater trochanter, and Ward’s triangle), and the lumbar spine (L1–L4). Assessments will be performed with participants in light clothing, barefoot, and without jewellery or removable metal. All DXA scans will be analyzed using a specific software (Physician’s Viewer, APEX System Software v.5.6.1.3, Hologic, Bedford, MA, United States).

##### Health-related quality of life

The EQ-5D questionnaire will be used for assessing participants’ health status, including a descriptive system formed by 5 dimensions and a visual analog scale (EQ-VAS) [65]. The 5 dimensions included in the descriptive system are: (1) mobility, (2) self-care, (3) usual activities, (4) pain/discomfort, and (5) anxiety/depression. The EQ-VAS scale consists of requesting participants to indicate their current health status from 0 ("*worst imaginable health status*") to 100 ("*best imaginable health status*").

##### Cognitive performance

The Trail-Making Test is a neuropsychological test with two parts [66]. In part A, the participant must connect the numbers from 1 to 25 in numerical order, while in part B, the subject must connect the dots in order while alternating letters (from A to L) and numbers (1 to 13), as quickly as possible without lifting the pencil from the paper. The Montreal Cognitive Assessment (MoCA, available at www.mocatest.org) is a single-page 30-item test completed in approximately 10 min that assesses visuospatial abilities, identification, memory, attention, language, 2-item verbal abstraction, delayed recall and orientation to time and place [67]. The Digit Symbol Substitution test is a pencil-and-paper psychomotor performance test [68] that requires the subject to match symbols to numbers according to a key located at the top of the page. The score is the number of right combinations of numbers and symbols that can be achieved in 2 min [69, 70].

##### Anxiety

The Zung Anxiety Self-Assessment Scale comprises 20 items related to anxiety symptoms (both psychological and somatic) [71]. Responses will be reported on a 4-point scale ranging from 1 (none or rarely) to 4 (most or all of the time).

##### Depression

The short form of the Yesavage Geriatric Depression Scale has proven to be a valid instrument for screening depression in older people [72]. This scale consists of 15 items with a yes/no answer pattern. Ten items show the presence of depression when the answer is positive (numbers 2, 3, 4, 6, 8, 9, 9, 10, 12, 14, 15), while the rest indicate depression when the answer is negative [73].

##### Physical activity and sedentary behavior

Physical activity levels and sedentary patterns will be assessed for 8 consecutive days using accelerometry (GeneActiv Original, Activinsights, UK) [74, 75]. The devices will be set to record data at 60 Hz and will be placed on the participant's non-dominant wrist. Additionally, they will receive a diary log to record when they remove the accelerometer. Furthermore, self-reported physical activity and time spent sitting will be measured using the International Physical Activity Questionnaire Short Form (IPAQ-SF) [76], which is a 7-item self-report questionnaire that calculates daily metabolic equivalents (METs) for the last 7 days, including vigorous activities, moderate activities, walking and sitting time. During the 48-week follow-up, an ad-hoc self-reported questionnaire will be used to assess questions related to exercise practice (see Supplementary File 1). The questionnaire will include the following questions: (1) *“Have you exercised on a regular basis during the last 6 months (from the post-intervention assessments until now)?”,* (2) *“What type(s) of exercise have you done during the last 6 months?”, (3) “What average of days a week have you exercised regularly?”, (4) “What average time (hours and/or minutes) have you exercised each day on a regular basis?”, (5) “What average intensity is best associated with the exercise you have done on a regular basis?”, (6) “Have you ever exercised under the supervision of a professional?”, (7) “Where have you usually exercised during the last 6 months?”, (8) “What type of equipment have you usually used for training during the last 6 months?”* and *(9) “Have you used any type of motivational strategy during the last 6 months?”*.

##### Sleep

The number of sleeping hours will be measured by accelerometry (GeneActiv Original, Activinsights, UK) for 8 consecutive nights, in addition to filling out a sleep diary to report nightly sleep periods [75, 77]. Additionally, the Pittsburgh Sleep Quality Index (PSQI) will be used to measure sleep quality during the last month [78]. The PSQI consists of 19 self-rated questions grouped into 7 component scores, including subjective sleep quality, sleep latency, sleep duration, habitual sleep efficiency, sleep disturbances, use of sleeping medications, and daytime dysfunction.

##### Biochemical markers

Blood samples will be obtained from the antecubital vein after an overnight fast of at least 12 h. Participants should refrain from moderate-to-vigorous physical activity for at least 72 h before the blood test. Analyses will include complete blood cell count, chemistry panel, lipid profile, electrolytes, and creatinine kinase. Samples will be analyzed immediately for routine clinical chemistry measurements and then placed in 500-µL aliquots to be frozen at -80ºC for further analysis.

##### Motivators and barriers to exercise

Participants’ perceived motivators and barriers to exercise will be assessed through the Benefits/Barriers to Exercise Scale [79], a 43-item instrument with a four-response Likert-type format: (1) strongly disagree, (2) disagree, (3) agree, and (4) strongly agree. Twenty-nine items are related to the benefits scale, while the remaining 14 are barriers. The total score of the instrument can range from 43 to 172 points, with higher scores indicating a more positive perception of exercise.

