**Methods:**

Participants (*n* = 120, aged 60–75 years) will be randomly allocated into five groups: 1-Control (CON), 2-Supervised exercise without motivational intervention (SUP), 3- Supervised exercise with motivational intervention (SUP +), 4- Unsupervised exercise without motivational intervention (UNSUP) and 5- Unsupervised exercise with motivational intervention (UNSUP +). Over 24 weeks, all exercise groups will participate in a multicomponent exercise program three times/week (performed in group classes at a center for SUP and SUP + , or home without supervision but with the help of a mobile app for UNSUP and UNSUP +), while the CON group will maintain their usual lifestyle. The motivational intervention (for SUP + and UNSUP + groups) will be based on the self-determination theory, including strategies such as phone calls, interactive workshops, motivational messages, informative infographics and videos. Primary outcomes will include safety, adherence, costs, and lower-body muscular function using a leg press machine. Secondary outcomes will include upper-body muscular function, physical and cardiorespiratory function, blood pressure and heart rate, body composition, health-related quality of life, cognitive performance, anxiety, depression, physical activity levels, sleep and sedentarism, biochemical markers, motivators and barriers to exercise. Assessments will be conducted at baseline, mid-intervention (*i.e.,* week 13), at the end of the intervention (*i.e.,* week 25), and 24 weeks later (*i.e.,* week 49).

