One of the factors that could moderate the effectiveness of exercise programs is adherence. In this regard, a recent meta-analysis by our research group showed that adherence to unsupervised exercise programs is usually low [29], probably due to a lack of motivation. Applying motivational strategies might help increase adherence to exercise programs, which could eventually result in greater training-induced adaptations [30–32]. Some studies have analyzed the impact of motivational strategies during exercise programs in older adults [33, 34]. However, these studies analyzed the influence of motivational strategies in supervised or unsupervised exercise interventions separately, but never before have they been examined in a single study.

The Promoting Training Programs for Health (PRO-Training) trial aims to cover all the abovementioned research gaps. The main goal of this RCT will be to determine the impact of supervision and motivational strategies on the safety, adherence, efficacy, and cost-effectiveness of different exercise programs for improving physical and mental health in older people.

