##### Adherence to the program

Adherence to the program will be calculated as a ratio between the sessions completed from those initially prescribed ([sessions completed/total sessions expected] × 100), where 0% indicates total non-adherence and 100% indicates full adherence [40]. The sports scientist will record adherence to the exercise program in the SUP and SUP + groups [41], while in the UNSUP and UNSUP + groups, it will be automatically registered through the mobile app [42].

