### Data collection and management

Outcomes will be assessed at baseline, mid-intervention (*i.e.,* week 13), at the end of the intervention (*i.e.,* week 25), and 24 weeks later (*i.e.,* week 49). At each measurement point –except for the mid-intervention measurement, which will only involve 1 session– participants must perform all assessments in 5 different days interspersed by at least 48 h and a maximum of 1 week. Trained assessors will conduct all assessments. A detailed scheme of the outcomes assessed in this study is shown in Figs. 1 and 3.

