### Statistical analysis

Data will be preferentially presented as mean ± standard deviation or as proportions for continuous and categorical variables, respectively. Data normality will be assessed by the Kolmogorov–Smirnov test and will be log-transformed in case of non-normal distribution. Baseline differences will be assessed through a one-way ANOVA. A two-way mixed ANCOVA (group [*i.e.*, CON, SUP, SUP + , UNSUP, and UNSUP +] x time [*i.e.,* baseline, mid, post-intervention, and follow-up assessments]) will be performed, adjusting for baseline values as well as for any other sociodemographic/descriptive variables that may differ between groups (*e.g.,* age, sex). Subsequent post-hoc tests will be conducted to determine which groups significantly differ. Effect sizes will be calculated to assess the magnitude of the differences [87]. Falls and fall-related injuries will be presented as rates/person (ITT analysis) and rates/person/year (± 30 days; PP analysis), and as numbers. Adverse events and dropouts will be compared between groups through Chi-squared tests. Differences in adherence rates will be analyzed using an ANOVA test. Correlation analyses will be used to assess associations between motivators, barriers, and adherence to exercise sessions. Whenever possible, statistical analyses will be performed on an intention-to-treat (ITT) basis (including all randomized participants). The potential effects of missing values and dropouts will also be explored using multiple imputation and sensitivity analyses [88]. As recommended, a complementary per protocol (PP) analysis will be performed (*i.e.,* including only those participants with valid data for baseline and post-intervention assessments and an adherence to exercise program of at least 80%) [89]. SPSS version 24.0 (IBM Corp., Armonk, NY) will be used for statistical analysis, and the significance level will be set at p ≤ 0.05 for all tests.

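### The adherence ANOVA is valid but uses no covariate, although baseline benefits and barriers scores should be available and could sharpen it at almost no cost

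*Protocol article*

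**What the plan says.** The abstract lists the primary outcomes: "Primary outcomes will include safety, adherence, costs, and lower-body muscular function using a leg press machine". Under Adherence to the program the measure is defined: "Adherence to the program will be calculated as a ratio between the sessions completed from those initially prescribed". It is a percentage of prescribed sessions, so it has no baseline value of its own and does not apply to the control arm, which has no sessions to complete.

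The Statistical analysis section gives the comparison in one sentence: "Differences in adherence rates will be analyzed using an ANOVA test". No covariate is named. The adjusted model in the same section is the group-by-time ANCOVA, described as "adjusting for baseline values as well as for any other sociodemographic/descriptive variables that may differ between groups". Among the secondary outcomes, Motivators and barriers to exercise says that "perceived motivators and barriers to exercise will be assessed through the Benefits/Barriers to Exercise Scale". For these scores the Statistical analysis section plans only this: "Correlation analyses will be used to assess associations between motivators, barriers, and adherence to exercise sessions".

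Three other statements bear on the point.
- Data collection and management sets the general schedule: "Outcomes will be assessed at baseline, mid-intervention", then weeks 25 and 49. Trial groups places random allocation after the baseline assessment.
- Confounding variables lists twelve baseline demographic and health items and says that they will serve as covariates in the analyses. Motivators and barriers are not on that list.
- The Background says that "adherence to unsupervised exercise programs is usually low [29], probably due to a lack of motivation".

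**The concern.** A covariate measured before allocation that predicts the outcome reduces the residual variance of a randomised comparison and takes out the part of any chance imbalance that it explains linearly. The repeated outcomes get this through their own baseline values. Adherence cannot, so another pre-allocation predictor is the only route.

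The protocol gives a reason to think that a motivation-related score might be such a predictor, and it should hold one for every participant. It keeps that score out of the arm comparison. The Randomization and blinding section states no stratification by motivation, and arms of about 24 leave room for chance differences. What is at stake is the precision of the contrasts for supervision and for motivational strategies on a primary outcome.

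There is also a loose end in the text. The Confounding variables section promises covariates for the analyses in general, while the adherence sentence carries none.

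**Working it through.** **The plan's own figure.** There is none for adherence. The Sample size section (100 participants, raised to 120) rests on a standardised mean difference of 0.43 for lower-body muscle power. It says nothing about the adherence SD, the expected difference or any correlation.

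**Inputs.**
- From the protocol: 120 participants, five arms, significance level 0.05.
- Assumed: equal allocation, so 120/5 = 24 per arm and N = 4 × 24 = 96 in the k = 4 exercise arms.
- Assumed: multiple correlation R, within arm, of the two baseline scores with adherence. The range shown is 0 to 0.5.
- Assumed, for the power illustration only: adherence SD of 25 percentage points, a 10-point motivation main effect (48 v 48) and a 15-point pairwise difference (24 v 24).

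**Variance ratio, adjusted to unadjusted.** With q = 2 covariates:

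ratio = (1 − R²) × [1 + q/(N − k − q − 1)] = (1 − R²) × (1 + 2/89) = (1 − R²) × 1.0225.

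The second factor is the price of estimating two slopes. The gain in effective sample size is 1/ratio − 1.

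| R | 1 − R² | ratio | gain in effective n |
|---|---|---|---|
| 0 | 1.00 | 1.02 | −2% |
| 0.2 | 0.96 | 0.98 | 2% |
| 0.3 | 0.91 | 0.93 | 7% |
| 0.4 | 0.84 | 0.86 | 16% |
| 0.5 | 0.75 | 0.77 | 30% |

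Break-even: 1 − R² = 1/1.0225 = 0.978, so R² = 0.022 and R is about 0.15.

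Leaving out the price factor would give 4%, 10%, 19% and 33%, which is too favourable.

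**Check with a single covariate.** The factor becomes 1 + 1/90. The ratio is 0.92 at r = 0.3 and 0.76 at r = 0.5, with break-even near r = 0.10. Simulation with 24 per arm gave 0.921 and 0.765.

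**Power (noncentral t, two-sided 0.05; 92 df unadjusted, 90 df adjusted).** The unadjusted SE is 25 × √(2/48) = 5.10 for the main effect and 25 × √(2/24) = 7.22 for a pair. The adjusted SE multiplies these by √ratio.

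| R | 10 points, 48 v 48 | 15 points, 24 v 24 |
|---|---|---|
| unadjusted | 49% | 54% |
| 0.2 | 50% | 55% |
| 0.3 | 52% | 57% |
| 0.4 | 55% | 60% |
| 0.5 | 60% | 65% |

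**Chance imbalance.** One standard error of the baseline difference between two arms is √(2/24) = 0.289 SD of the score. The expected shift in the unadjusted adherence difference is 0.289 × R × 25, which is 1.4 points at R = 0.2 and 3.6 points at R = 0.5. Both are at most half of the pairwise SE of 7.22, which already allows for them.

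**The case against.** The strongest reply is that nothing here is wrong. An unadjusted comparison of randomised arms is valid, chance imbalance is not bias, and a condensed article may leave the choice of covariates to an analysis plan that is not shown. The first two parts stand in full. The third stands only partly, because the article does not leave the method open: it names an ANOVA for this outcome.

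A second reply is that the Confounding variables section already promises covariates, so one cannot say that adjustment is confined to the group-by-time outcomes. That is fair. But its list omits motivators and barriers, and the adherence sentence takes up none of it. The two sections need reconciling.

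A third reply concerns the choice of score. The trial also measures exercise motivation with BREQ-3 and psychological needs with BPNES. Nothing in the protocol ranks the Benefits/Barriers scores above these. This also stands. The case for the two scores is only that the protocol itself singles out motivators and barriers for association with adherence.

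A reader might infer three stronger things:
- **That precision is certainly being lost.** The protocol gives no correlation, and below about R = 0.15 there is nothing to gain.
- **That the trial expects these scores to drive adherence.** The Background remark is hedged, concerns unsupervised programs, and speaks of motivation rather than this scale. The analysis section plans only to examine associations.
- **That the baseline timing of this scale is stated outright.** It follows from the general schedule and from allocation after baseline. The figures with the assessment schedule are not shown.

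**Conclusion.** The point holds as a missed opportunity for precision on a primary outcome, not as an error. The stated ANOVA would give a valid test and estimate, but it may be less precise than the collected data allow.

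The balance of risk favours adjustment: a loss of about 2% in variance at worst, against a gain worth about 2% to 30% more participants for R between 0.2 and 0.5. At R = 0.3 the improvement is modest, about three percentage points of power in the illustrations. These sizes rest on equal arms of 24 without dropout and on an assumed R. The power figures also rest on an assumed SD and assumed differences. Adjustment removes only the part of the variance and imbalance that the measured scores explain linearly.

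**What to change.** In Statistical analysis, replace the adherence sentence by a linear model of adherence on arm, over the four exercise arms, with the baseline benefits score and the baseline barriers score as two covariates. Name them in advance and keep them whatever baseline balance is observed. Use only scores taken before allocation, since the interventions can change later ones. Report the unadjusted ANOVA as a sensitivity analysis. In the same edit, say whether any variable listed under Confounding variables enters this model, so that the two sections agree.

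The cost is a sentence or two of wording and two of 92 residual degrees of freedom. No new data are needed if the scale is taken at baseline as the general schedule implies. The change should be made before anyone sees outcome data by arm, because a covariate chosen afterwards would look data-driven.
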